### 2.16. Study Hypothesis

Firstly, UPDRS scores are expected to be significantly lower in group A1 and A2 than in group S1 and S2 after stage 1, and the scores show a trend from low to high in groups A2, A1, S2, and S1 after stage 2. Next, the change in the slope of the weekly UPDRS scores will be compared among the 4 groups. We expect a slower rate of deterioration (i.e., increase in UPDRS scores) with the iTBS intervention than with the pseudo-stimulation group. The mean total UPDRS score deteriorates less from baseline to week 28 in the early-start groups than in the delayed-start groups. For the changes in slope of UPDRS scores between weeks 14 and 28, the early-start groups are expected to respond better than the delayed-start groups.

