### 2.15. Outcome Measures

According to the results of previous large delayed-start design disease-modifying drug studies, the neuroprotective effect can be commonly reflected by the difference in the changes in the UPDRS score before and after treatment between groups [22,39]. In an NET-PD study, the primary outcome is the differences in changes in UPDRS scores in the four groups before and after the iTBS intervention. As a secondary outcome, we will evaluate the effects of iTBS treatment on clinical symptoms, motor symptoms such as gaiting and postural balance, and non-motor symptoms such as mood, cognition, olfaction, and sleeping condition in PD patients. As a neuro-modulation intervention study, EEG, EMG and MRI images can also be visualized to indicate the functional activity status of the brain. The safety of the treatment will be assessed using a self-administered side effect scale. Additionally, self-administered side effects scales will be used to assess iTBS safety.

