### 2.17. Sample Size and Statistical Analysis

With reference to data from previous studies published in relevant journals, a total of 60 PD patients are proposed to be enrolled in this single center study. The sample size of this study was calculated based on the improvement in the UPDRS scale after 28 weeks of treatment and differences between groups. Calculations are performed using PASS (Power Analysis and Sample Size) 2008 software (UT, OH, USA), assuming a four-point reduction in the UPDRS at the end of treatment in A1, a five-point reduction in A2, a two-point reduction in S1, and a four-point reduction in S2, with a standard deviation of 2, a test level of 0.05, and a degree of certainty of 0.9 yielded for 13 subjects per group. Considering that the patient dropout rate may be about 10% [24,40], the final plan is to enroll n = 15 cases in each group for n = 60 cases in total. The minimum sample size required to meet the hypothesis of this clinical study is 60, and actual samples of 60 cases or more are in accordance with the clinical study design principles and statistical requirements.

Statistical analysis applies SPSS 20.0 for processing; MRI, EEG, and EMG data are processed on MATLAB platform (Math Works Inc., Natick, MA, USA). All statistics are performed using two-sided tests, and α = 0.05 is the cut-off point used to decide whether the hypothesis is statistically significant. Between-group comparisons of quantitative data will be performed using analysis of variance (ANOVA) or Wilcoxon rank sum test depending on the distribution of the data. A paired *t*-test or Wilcoxon signed-rank test will be used for comparison before and after treatment. Categorical data are tested by chi-square test or exact probability method (if the chi-square test is not applicable).

To compare the changes in UPDRS scores before and after the iTBS intervention at each time point, mainly comparing the differences in their means, two-way repeated-measures ANOVA was used to compare the main effects and the interaction effects between the two for different groups and follow-up points (baseline, week 14, week 28), and post hoc analysis was performed using the Bonferroni test to compare the differences between each follow-up point and baseline scores.

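### No single UPDRS contrast, visit or success rule is named as deciding neuroprotection, so a week-14 difference alone could be claimed as success

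*Protocol article*

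**What the plan says.** Section 2.1 makes the neuroprotective effect of iTBS the primary objective. Section 2.15 defines the outcome: "the primary outcome is the differences in changes in UPDRS scores in the four groups before and after the iTBS intervention". It names no visit, contrast or test.

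Section 2.16 then sets out five UPDRS expectations:

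1. After stage 1 (week 14): "Firstly, UPDRS scores are expected to be significantly lower in group A1 and A2 than in group S1 and S2 after stage 1".
2. After stage 2, scores ordered A2, A1, S2, S1 from low to high.
3. Weekly slopes compared among the groups, with slower worsening under active than sham stimulation.
4. "The mean total UPDRS score deteriorates less from baseline to week 28 in the early-start groups than in the delayed-start groups".
5. A better slope between weeks 14 and 28 in the early-start groups.

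Section 2.17 adds a further analysis at baseline, week 14 and week 28: "two-way repeated-measures ANOVA was used to compare the main effects and the interaction effects between the two for different groups and follow-up points". On the error level it says "All statistics are performed using two-sided tests" and "α = 0.05 is the cut-off point used to decide whether the hypothesis is statistically significant". Bonferroni is mentioned once, for post hoc comparison of follow-up visits with baseline. The same section bases the sample size on UPDRS improvement after 28 weeks and the differences between groups.

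**The concern.** These results do not mean the same thing in a delayed-start trial. During stage 1 only A1 and A2 receive active stimulation (section 2.2), so a week-14 difference may be entirely symptomatic. The Introduction gives removal of the symptomatic effect as the reason for choosing this design. The comparison that bears on neuroprotection is the one at week 28, when all arms have had active treatment and differ in when it began.

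The results can also disagree. A trial positive at week 14 and null at week 28 would meet expectation 1 and fail expectation 4, and the text does not say whether that is a success. If one favourable result among several may be picked out afterwards, the error level for the primary claim is no longer 5%.

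**Working it through.** **1. The plan's own sample size.** Inputs from section 2.17 are reductions of 4 (A1), 5 (A2), 2 (S1) and 4 (S2), and "with a standard deviation of 2, a test level of 0.05, and a degree of certainty of 0.9 yielded for 13 subjects per group".

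- The grand mean is 15/4 = 3.75. The squared deviations are 0.0625 + 1.5625 + 3.0625 + 0.0625 = 4.75.
- For a one-way four-group F test, λ = n × 4.75 / 2². At n = 13, λ = 15.44 on 3 and 48 df.
- Power is 0.872 at n = 12 and 0.901 at n = 13. Then 13/0.9 = 14.4, rounded up to 15 per arm, 60 in total.

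The stated figure is therefore reproduced as an omnibus F test on the 28-week change.

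**2. What that omnibus test responds to.** The 4.75 splits into three orthogonal parts.

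| Component | Means compared | Sum of squares |
|---|---|---|
| Early vs delayed | 4.5 vs 3.0 | 4 × 0.75² = 2.25 |
| Single vs double | 3.0 vs 4.5 | 4 × 0.75² = 2.25 |
| Interaction | (5 − 4) − (4 − 2) = −1 | 1/4 = 0.25 |

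Session frequency contributes as much as start time. A significant omnibus test would not by itself show an early-start advantage, and it is none of the five expectations.

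**3. False-positive chance under each possible success rule.** The documents give no visit correlation, and they do not assign a test to each expectation. Both are assumptions here. The simulation had no effect in any arm, 13 or 15 patients per arm, visits at weeks 0, 2, 14, 16 and 28, equal or autoregressive correlation from 0.3 to 0.9, and each expectation tested as a two-sided contrast. Each test alone rejects in about 5%.

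| Rule | Chance under no effect |
|---|---|
| One named test | 5% |
| Any of five; 1 and 2 on change from baseline | about 13–16% |
| Any of five; 1 and 2 on raw scores | about 17–19% |
| Any of five, if independent: 1 − 0.95⁵ | 22.6% |
| Any of five, favourable direction only | about 7–10% (one test: 2.5%) |
| Any of five, or any of three ANOVA F tests | about 24–28% |
| All five required | 0.1% or less |

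**4. Power of the early-versus-delayed contrast at week 28.** The difference is 4.5 − 3.0 = 1.5, with SD 2.

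- As a contrast within the four-group ANOVA, SE = 2/√n. At n = 13, SE = 0.555, the noncentrality is 2.70 on 48 df, and power is 75%. At n = 15, SE = 0.516, the noncentrality is 2.90 on 56 df, and power is 81%.
- As a two-sample t-test on pooled arms, the differences between arms inside each pool raise the SD to about 2.16. Simulated power is about 70% at 13 per arm and 77% at 15.

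**The case against.** Three points on the other side have force.

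- **The text does point to week 28.** The trial is sized on that visit, section 2.14 treats it as the experiment's endpoint, and the repeated-measures paragraph echoes the primary-outcome wording. It would be wrong to say that the plan gives no pointer. It remains a pointer to a visit, not to a contrast, and the sized test does not separate start time from session frequency.
- **The expectations may be meant jointly.** They stand under a singular heading and read as one pattern. Only the first uses the language of significance; the second speaks of a trend. Under a joint rule the error is not inflated. That five separate confirmatory tests are intended is an interpretation.
- **Hierarchy is often left to an analysis plan.** That would excuse missing detail. Here the article's own outcome, hypothesis and analysis sections set several competing claims beside one primary outcome without saying which governs.

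A reader might infer that the trial's false-positive rate is some definite figure, such as 17%. The documents do not support that. Such a figure needs an any-one-succeeds rule, chosen test forms and an assumed correlation, none of which is stated. It also counts results that favour delayed start, which could not be reported as neuroprotection.

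**Conclusion.** The point holds as a gap in what the protocol fixes: no decisive UPDRS contrast, visit or success rule is named for the primary objective. As written, a week-14 difference that may be purely symptomatic could be presented as meeting it.

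The effect on the error rate is conditional. It is roughly 13–19% two-sided if any one of the five expectations suffices, about 7–10% against 2.5% if only favourable results count, more if the F tests count, and not inflated if all must hold. These ranges rest on normal scores and the assumed correlations and test forms. The spread matters more than any one value in it, because without a success rule the error rate cannot be determined. Nor can the stated 90% power be read as power for the neuroprotection comparison; it belongs to the omnibus test.

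**What to change.** In sections 2.15 to 2.17:

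- Name the change in total UPDRS from baseline to week 28, A1+A2 versus S1+S2, as the test that decides neuroprotection at two-sided 0.05.
- Let it stand alone, or test it only after a significant week-14 early-versus-delayed difference, in a fixed sequence with both steps at two-sided 0.05.
- State that a week-14 difference alone does not meet the primary objective.
- Label the four-group ordering, the slope comparisons, single versus double sessions, and the omnibus main-effect and interaction tests as supportive or exploratory.
- Restate the power for the chosen test.

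The wording takes a few sentences and needs no new data, and only two patients were enrolled at the time of writing (section 3). The costs are real, though. The ordering, slope and session-frequency results lose confirmatory status, as does the four-group comparison on which the trial was sized. On the protocol's own means and SD, power for the named contrast is about 70–75% at 13 completers per arm and about 77–81% at 15. Requiring the week-14 step can only lower this, and the protocol gives no week-14 assumption from which to say by how much. The sponsor should either accept and report the lower power or revisit the sample size.

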### 2.2. Study Design

NET-PD is a 2-year prospective single-center, double-blind, multi-arm, delayed-start, sham-controlled trial. The study is conducted in two stages—the pseudo-controlled and active-treatment stage—with each stage consisting of a 2-week intensive phase and a 12-week maintenance phase, for a total of 14 weeks. The intensive period involves daily or twice-daily iTBS (or pseudo-stimuli) per week, for a total of 10 or 20 sessions, and the maintenance period consists of 12 weeks of iTBS (or pseudo-stimuli) once or twice a day, 2 days a week, for a total of 24 sessions in the single-stimulation group or 48 in the double group. In stage 1 (pseudo-controlled stage), patients are randomly assigned to one of four intervention groups in a 1:1:1:1 ratio: early-start single iTBS group (A1), early-start double iTBS group (A2), delayed-start single iTBS group (S1), and delayed-start double iTBS group (S2). The early-start groups conduct active iTBS throughout, whereas the delayed-start groups use pseudo-stimuli in the first stage and start using iTBS in the second stage. The only difference between the single- and double-stimulation group is the number of sessions per day: once daily for the single group and twice daily for the double group. In stage 2 (active treatment stage), participants in A1 and A2 continue to receive the same iTBS protocol as the first stage, while those in S1 and S2 start to receive active iTBS. All patients are required to have a detailed follow-up clinical assessment and electrophysiology record at baseline, 2 weeks, 14 weeks, 16 weeks, and 28 weeks. MRI and peripheral blood are collected at baseline, 14 weeks, and 28 weeks (Figure 1, Table 1). Each patient will spend 7 months in this study and the total duration of the research will be approximately 2 years, from July 2022 (first in) to December 2024 (last out) (Figure 2).

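### The week 28 hypotheses predict a direction and an order of the arms, but the stated UPDRS tests are unordered between arms and the post hoc tests compare visits with baseline

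*Protocol article*

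**What the plan says.** Section 2.16 (Study Hypothesis) expects that after stage 2 "the scores show a trend from low to high in groups A2, A1, S2, and S1 after stage 2". It also expects the early-start arms to have worsened less than the delayed-start arms between baseline and week 28. Both predictions are directional comparisons between arms.

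Section 2.17 (Sample Size and Statistical Analysis) gives these tests:

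- In general: "Between-group comparisons of quantitative data will be performed using analysis of variance (ANOVA) or Wilcoxon rank sum test", depending on distribution.
- For UPDRS: "two-way repeated-measures ANOVA was used to compare the main effects and the interaction effects" of group and visit (baseline, week 14, week 28).
- Post hoc: Bonferroni tests of each follow-up visit against baseline. No post hoc comparison between arms is named.

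For the sample size, the same section takes the early-start arms to improve by 4 points (A1) and 5 points (A2). Its figures for the delayed-start arms are "a two-point reduction in S1, and a four-point reduction in S2". The SD is 2 and the target power 0.9, which leads to 13 patients per arm. Tests are two-sided at 0.05. A1 and S2 therefore have the same assumed reduction, although section 2.16 places A1 ahead of S2.

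**The concern.** An omnibus F test asks whether the arms differ at all. Its p-value does not change if the arm means are exchanged, so a significant result fits the predicted order, its reverse or any other arrangement equally well. Visit-versus-baseline tests show that patients changed over time; they do not compare one arm with another.

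Followed as written, the plan would leave the predicted order, and the advantage of early over delayed start at week 28, to be read off the arm means after a significant F. The primary outcome in section 2.15 is the difference in UPDRS change among these four arms, so this affects the main comparison. This is more than detail left to a fuller document: section 2.17 does name a post hoc step, and points it at visits instead of arms.

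**Working it through.** **Inputs (section 2.17, allocation from section 2.2).** Reductions in the order A2, A1, S2, S1 are 5, 4, 4, 2. SD 2, two-sided 0.05, 13 per arm, equal allocation. The outcome is taken as change at week 28, analysed as a one-way comparison of four arms. The power of the repeated-measures version would also need the correlation between visits, which the article does not give.

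**1. The plan's own sample size.**
- Mean reduction = 15/4 = 3.75.
- Sum of squared deviations = 1.25² + 0.25² + 0.25² + 1.75² = 4.75.
- Noncentrality = n × 4.75 / SD² = 13 × 4.75 / 4 = 15.44, on 3 and 48 df.
- Power = 0.901 at 13 per arm and 0.872 at 12.

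So 13 per arm is reproduced by an unordered four-arm F test.

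**2. What the F test says about order.** The noncentrality depends only on the set of means, not on which arm has which. Reversing the assignment to 2, 4, 4, 5 again gives 0.901. In simulation under the plan's means at 13 per arm, the observed means fall in the predicted order in 41% of trials, and in 42% of the trials with a significant F. Significance adds almost nothing about order.

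**3. A linear trend contrast, weights 3, 1, -1, -3 for A2, A1, S2, S1.**
- Estimate = 3×5 + 1×4 - 1×4 - 3×2 = 9.
- SE = 2 × √(20/13) = 2.48.
- Noncentrality = 9/2.48 = 3.63 on 48 df, so power = 0.945.
- It reaches 0.90 with 11 per arm; the F test needs 13.

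The two-sided contrast would also be significant under the reverse order, but with the opposite sign. That sign is the information the F test lacks.

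**4. What the trend contrast is made of.** (3, 1, -1, -3) = 2 × (1, 1, -1, -1) + (1, -1, 1, -1): twice early versus delayed plus double versus single. Under the plan's means:
- Early versus delayed: (5+4) - (4+2) = 3.
- Double versus single: (5+4) - (4+2) = 3.
- Each has SE = 2 × √(4/13) = 1.109, noncentrality 2.70 and power 0.755.

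If only the number of daily sessions mattered (5, 2, 5, 2), early versus delayed is zero, yet the trend estimate is 15 + 2 - 5 - 6 = 6, noncentrality 2.42, and it is significant 66% of the time. It therefore needs its components beside it.

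**5. How far the power gain extends (13 per arm).** The first row is the plan's case; the others are illustrations.

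| Reductions A2, A1, S2, S1 | SD | F test | Trend contrast |
|---|---|---|---|
| 5, 4, 4, 2 | 2 | 0.901 | 0.945 |
| 5, 4, 4, 2 | 3 | 0.542 | 0.659 |
| 5, 4, 3, 2 | 2 | 0.916 | 0.977 |
| 5, 2, 2, 2 | 2 | 0.976 | 0.945 |
| 4, 4, 4, 2 | 2 | 0.711 | 0.659 |

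The last two rows do not contradict the predicted direction, and there the F test is stronger.

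**6. Adjacent steps under the plan's means, unadjusted 0.05.** Power is 0.24 for A2 versus A1, 0.05 for A1 versus S2 (equal means, so only the false-positive rate) and 0.71 for S2 versus S1.

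**The case against.** The strongest reply is that outcome, sample size and test already agree. Section 2.15 states the primary outcome without an order, the group-by-visit ANOVA addresses it, and 13 per arm is what an F test needs. In section 2.16 statistical significance is attached to the stage 1 comparison; the stage 2 order reads as an expected pattern, one of several. Follow-up contrasts may be set out in a fuller document. The Wilcoxon rank sum test is also named, and it is directional when applied to a pair of arms.

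Much of this stands. The F test is a sound test of any difference and has its intended power, 0.943 with all 15 enrolled per arm. But the order and the early-start advantage at week 28 are stated hypotheses, the stated post hoc step does not address them, and no pair of arms is named for a rank sum test. That test is not an ordered four-arm test either.

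A reader might infer two stronger claims. The first is that the F test is the weaker test for an ordered pattern in general. The figures do not support this: the gain is 4.4 percentage points under the plan's means and reverses for some single-step patterns. The second is that the trend contrast should simply replace the F test and would establish the order. It would not: it is significant 66% of the time under a pure session-number effect, and 88% of the time with A1 and S2 misordered (5, 3, 4, 2).

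**Conclusion.** The point holds as a mismatch between hypothesis and test. Section 2.16 makes directional between-arm predictions at week 28; section 2.17 states an unordered ANOVA and visit-versus-baseline post hoc tests, so no stated test supports the direction or order. The main ground is the F test's blindness to order. Power is secondary: 0.945 against 0.901, or two patients per arm, given the plan's means, SD 2 and a one-way analysis of week 28 change.

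The planning figures have a related inconsistency: equal reductions in A1 and S2 contradict the predicted order, and under them no test has power for that step.

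The documents do not support reading this as an invalid or underpowered primary analysis. The change is advisable, not essential.

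**What to change.** In section 2.17:

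1. Keep the omnibus F test for any difference among the arms.
2. For the week 28 hypotheses, replace the visit-versus-baseline tests with pre-specified contrasts on UPDRS change from baseline to week 28: the linear trend (3, 1, -1, -3 for A2, A1, S2, S1), always reported with early versus delayed (A1+A2 v S1+S2) and double versus single (A2+S2 v A1+S1), so that a session-number effect is not read as an early-start effect.
3. State that a significant trend does not prove each adjacent step and is not by itself evidence of neuroprotection.
4. Reconcile the equal 4-point reductions for A1 and S2 with the order in section 2.16.

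The cost is a few sentences, with no new patients, visits or data. The article reports two patients enrolled, so the wording can be settled before outcomes are analysed. There are two downsides. The trend contrast is less sensitive than the F test to non-monotone and some single-step patterns (0.945 v 0.976 for 5, 2, 2, 2). Each component has power of only about 0.755 at 13 per arm, so a non-significant component should not be read as no effect.

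### The week 14–28 slope hypothesis starts at the delayed arms' switch to active iTBS and predicts the early arms do better, so it would probably fail even if iTBS is protective, and it conflicts with the plan's own week-28 figures

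*Protocol article*

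**What the plan says.** Section 2.2 gives the timetable, with "each stage consisting of a 2-week intensive phase and a 12-week maintenance phase, for a total of 14 weeks". It says that "the delayed-start groups use pseudo-stimuli in the first stage and start using iTBS in the second stage". In stage 2 the early arms carry on with their active protocol unchanged, "while those in S1 and S2 start to receive active iTBS". Week 14 is therefore the delayed arms' last assessment before active treatment.

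Section 2.16 expects A1 and A2 to be significantly lower than S1 and S2 on UPDRS after stage 1, less deterioration from baseline to week 28 in the early arms, and then: "For the changes in slope of UPDRS scores between weeks 14 and 28, the early-start groups are expected to respond better", the comparison being with the delayed arms. It also says that "the change in the slope of the weekly UPDRS scores will be compared among the 4 groups".

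Section 2.17 assumes UPDRS reductions at the end of treatment of 4 (A1), 5 (A2), 2 (S1) and 4 (S2), with SD 2. Its repeated-measures ANOVA uses baseline, week 14 and week 28. UPDRS is also scheduled at weeks 2 and 16 (section 2.14, Table 1).

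The Introduction justifies the delayed-start design as a way to remove the symptomatic effect of treatment from the comparison.

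**The concern.** From week 14 to week 28 all four arms are active, but only S1 and S2 are having their first active intensive course. Any symptomatic benefit of starting iTBS falls inside this window for them; for A1 and A2 it fell in stage 1. A better early-arm slope here means that the gap widens after the controls start treatment. In a delayed-start design, lasting protection shows instead as a gap that remains at week 28 and is not closing once the symptomatic effect has set in.

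The hypothesis thus brings back, against the early arms, the effect that the design is meant to remove. Neuroprotection is the primary objective (section 2.1), and this is one of the stated tests of it. A trial of a protective treatment could show the reverse of the prediction, and a reader could take that as evidence against protection.

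**Working it through.** **1. The plan's own figure.** The assumed changes are −4, −5, −2, −4, with mean −3.75. The squared deviations are 0.0625, 1.5625, 3.0625 and 0.0625 (sum 4.75). Cohen's f = √(4.75/4)/2 = 0.545. One-way four-group ANOVA at α = 0.05 has power 0.872 with 12 per arm and 0.901 with 13. For 10% dropout, 13/0.9 = 14.4, rounded up to 15, and 15 × 4 = 60. The sample size reproduces, so the week-28 means and SD can be taken as intended.

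**2. What the slope measures under protection.** Let r be progression in points per week without treatment, p the reduction in that rate on active iTBS, and s a symptomatic benefit (over sham) that appears once active iTBS starts. Expected changes from baseline are:

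| | Week 14 | Week 28 |
|---|---|---|
| Early | 14(r − p) − s | 28(r − p) − s |
| Delayed | 14r | 14r + 14(r − p) − s |

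Early minus delayed is D14 = −14p − s and D28 = −14p. The difference in week 14–28 change is D28 − D14 = **+s**, whatever p is. With the pooled week-28 gap of 1.5 points, s = 1 gives D14 = −2.5 and a slope difference of 1/14 = 0.07 points per week in favour of the delayed arms; s = 2 gives −3.5 and 0.14.

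If protection in the early arms' second stage is stronger by q points per week than in the delayed arms' first active stage, the difference becomes s − 14q. The early arms do better only if 14q > s.

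**3. Chance of the predicted result.** Neither s nor the SD of the week 14–28 change is in the article, so both are assumptions. Noncentral t, two-sided 0.05, early v delayed pooled, 30 v 30, constant-rate protection:

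| s | SD of change | P(early significantly better) | P(delayed significantly better) |
|---|---|---|---|
| 0 | any | 0.025 | 0.025 |
| 1 | 1.5 | <0.0001 | 0.72 |
| 1 | 2 | 0.0001 | 0.48 |
| 1 | 3 | 0.0006 | 0.25 |
| 2 | 2 | <0.0001 | 0.97 |

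**4. Consistency with section 2.17.** This step needs no model of protection. A better early slope requires the week-14 gap to be smaller than the week-28 gap (equal expected baselines by randomisation). The smallest observed week-14 gap that reaches significance, taking the section 2.17 SD of 2 to hold at week 14, is:

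- pair, 13 per arm: t(0.975, 24) × 2 × √(2/13) = 1.62 (1.50 with 15 per arm);
- pooled, 26 v 26: t(0.975, 50) × 2 × √(2/26) = 1.11 (1.03 with 30 v 30).

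| Contrast | Week-28 gap | Week-14 gaps that fit both expectations |
|---|---|---|
| A1 v S2 | 4 − 4 = 0 | none |
| A2 v S2 | 5 − 4 = 1 | none (needs at least 1.6) |
| A1 v S1 | 4 − 2 = 2 | about 1.6 to 2 |
| A2 v S1 | 5 − 2 = 3 | about 1.6 to 3 |
| Pooled | 4.5 − 3 = 1.5 | about 1.1 to 1.5 |

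For A1 v S2 the SD plays no part: any A1 advantage at week 14 has to be lost by week 28 for the two to end equal.

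**The case against.** A reader might infer that the hypothesis must fail, or that the trial cannot show neuroprotection. The article supports neither.

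- **Failure is conditional.** No symptomatic effect size and no week-14 means are given. If protection grew with time on treatment by more than s, the early arms could have the better slope. The Introduction's hope of reversing neuronal loss does not exclude this, although no such model is stated.
- **Pooled, the expectations can coexist.** The window is narrow but not empty, and the A1 v S1 and A2 v S1 pairs are compatible too. The A1 v S2 conflict depends on the section 2.17 reductions; the section 2.16 ordering itself puts A1 below S2 after stage 2.
- **No decision rule rests on this slope.** The sample size uses week-28 changes, section 2.17 specifies an ANOVA on means, and the baseline-to-week-28 contrast in section 2.16 is a sound delayed-start comparison. Nowhere does the article say that protection is rejected if the slope prediction fails.
- **Two tempting additions are weak.** The phrase about weekly scores can be read as points per week. The three visits in section 2.17 belong to the ANOVA, so it does not follow that the slopes use only two points; that detail may be left to the analysis plan.

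All of this stands. It limits the certainty and reach of the point but does not correct the direction of the prediction.

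**Conclusion.** The point holds in conditional form. The window opens at the switch to active treatment, and the predicted direction is the one that constant-rate protection does not produce: the expected difference is zero without a symptomatic effect and +s against the early arms with one. The prediction would then be confirmed in 2.5% of trials at s = 0 and in at most about 0.1% at s = 1 (SD of change 1.5 to 3). These figures assume constant-rate protection and a symptomatic effect that is complete by week 28 in the delayed arms.

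Independently of that model, the prediction contradicts the plan's figures for A1 v S2, contradicts them for A2 v S2 if that pair differs significantly at week 14, and leaves only about 1.1 to 1.5 points pooled. It is a wrongly directed test of the primary objective and should be corrected. The week-28 contrast and the sample size are unaffected.

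**What to change.** In section 2.16, replace the week 14–28 slope hypothesis with:

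1. *Main contrast:* superiority of early over delayed start in UPDRS change from baseline to week 28, which is already stated there.
2. *Supportive:* the gap is not closing. Test non-inferiority of early v delayed arms on the change from week 16 to week 28, with a margin stated before the data are seen.

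Add that a better delayed-arm slope over weeks 14–28 will not be read as evidence against neuroprotection, and reconcile the section 2.16 expectations with the section 2.17 means for A1 and S2. Describing slopes as points per week from the scheduled visits would be a useful edit.

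The cost is wording and one margin. Both UPDRS visits are already scheduled, and the article reports only two patients enrolled.

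The downside is precision. The new test rests on two visits and assumes that most symptomatic onset has occurred by week 16, although maintenance sessions follow. With an assumed SD of change of 2 and 26 v 26, the 95% interval half-width is 2.009 × 2 × √(2/26) = 1.1 points (0.8 at SD 1.5, 1.7 at SD 3), against a pooled week-28 gap of 1.5. It should therefore be labelled supportive.
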